**Figure 1 F1:**
[figure not shown]
A conceptual framework showing the linkages of WASH and food safety with stunting at the household level. WASH, water, sanitation and hygiene.

In theory, access to adequate WASH facilities enables appropriate drinking water, hygiene and food safety practices, contributing to reduction in transmission of foodborne and waterborne pathogens and improving nutrient uptake, and ultimately child growth and development.^20^ Drinking water may be contaminated at the point of supply, or through transport and storage.^15 16^ The availability of clean water is critical for optimal hygiene practices,^10^ to address contamination by human and animal faeces,^22^ and to prepare food hygienically. Sanitation facilities can enable safe faeces disposal, especially those of young children, which can be particularly pathogenic.^23^ Faecal contamination can also come from the presence of domestic and wild animals or pests inside the household or in surrounding spaces.^24^ It is expected that these sources of infection become more important as a child starts crawling and interacting with their environment. As such, understanding of the determinants of food and hygiene practises in the household is key to improving infant health and nutrition.^25^

Along with direct exposure, there is also an indirect route from water supply and sanitation facilities to childhood malnutrition, which operates through the opportunity costs of resource use. The time carers have to observe, correct, and address unhygienic behaviour, and the scarcity of time in relation to competing activities that need to be done by carers in the home or workplace, may also be detrimental for children’s nutritional outcomes.^26^ For example, it is typically women and older children, both of whom are more likely than others to be carers of young children, who spend time fetching water, engaging with animal fodder and collecting firewood. This may occur at the expense of adequate childcare and feeding, food preparation, education or rest.^27^ When drinking water needs cannot be met affordably, households may need to purchase less food in order to afford enough water to drink. This kind of trade-off is clearly more prevalent for the poorest households, for whom malnutrition is also likely to be highest.

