### Data collection

This WASH and food safety data collection protocol focuses on three areas: exposure pathways to wider environmental pathogens, foodborne hazards and waterborne hazards. Four data collection tools for the household-level have been developed, namely: (1) a module for WASH and food safety to be included to the cohort questionnaire-based interviews (see online supplemental appendix 1); (2) spot-checks (see online supplemental appendix 2); (3) biological sampling and (4) direct observation (see online supplemental appendix 3). The interviews and spot-checks take place simultaneously during home visits at 9, 12 and 18 months after birth. Data will be collected throughout the different seasons. Direct observation and biological sampling are conducted during a separate subsequent visit at each time point, in a subsample of the cohort. No additional inclusion or exclusion criteria were considered in the selection. Food and water samples are kept to a minimum for the analysis required, namely half filling a 50 mL Falcon tube with food served to the child, and the measure of the container in which the child is normally given drinking water, respectively.

10.1136/bmjpo-2022-001695.supp1Supplementary data

The food safety component of the data collection focuses on nutrient-rich foods with the potential to alleviate stunting, particularly on animal source foods (ASFs). This is due to their important nutritional profile,^29^ their documented potential to alleviate stunting^30–33^ and their high food safety risk profile. Selected ASFs will be considered at each country, according to their relevance.

Trained enumerators collect data using electronic tablets in all study households, as summarised in table 2. The direct observation tool is recorded on paper and enumerator positioning and previous rapport creation are used as ways to minimise bias. Privacy is maintained by stopping the direct observation on the respondent’s request. Data collection tools developed in English are translated into local languages and backtranslated into English to check for accuracy, and piloted in the field.

**Table 2 T2:** Summary of the integrated study methods and tools used to assess WASH and food safety at the household level

Tool	Description	Sample size

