Questionnaire-based interview	Mothers are asked about infant and young child feeding practices, household food expenditure and the main household decision-makers and influencers of these activities. Physical activity questionnaires ask mothers about the times spent on work and housekeeping including collecting water, fodder and fuel. Furthermore, there are questions on water sources, water security, sanitation and handwashing. Other questions focus on the practices of acquisition, transport, storage, preparation of ASF and the points of potential contamination in the household. Finally, other questions refer to the presence and behaviour of animals and potential transmission pathways associated with close proximity to animals, such as direct contact between animals and children or food. The hazards and risks prior to arrival of ASFs in the household are elucidated in a separate component, at the value chain level (see Cooper *et al* in this supplement).	Whole cohort (500 households per country)
Spot-check	Enumerators observe behavioural issues alongside the interview questionnaire. The data are recorded using a check list on the availability and type of sanitation facilities available at the households (eg, the place for defecation and proximity), handwashing infrastructure (eg, location, availability of water and soap), presence of animals (eg, livestock, pests), food storage facilities and practices (eg, functioning refrigerator) and food preparation (eg, easy to clean equipment).	Whole cohort (500 households per country)
Direct observation	Enumerators stay at the household for 3 hours around a feeding event, observing the mothers perform their daily activities and taking a passive approach to blend into the background in order to better observe hygiene related behaviours. Structured observation include activities related to water collection and storage, as well as personal, environmental and food hygiene (food preparation, storage, child feeding, handwashing and animal contact). This data collection method is a gold standard for actual observation of behavioural practices.	Subsample (approximately one-third of full cohort in each country)

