Biological sampling and testing	Enumerators collect samples of stored water, foods to be consumed by the children (as close to the feeding of the child as possible) and a swab of the main food preparation area at the households. Samples of hands rinse are optional. The samples are stored in a coolbox and transported to a specialised laboratory for analysis. The samples are processed in-country and tested for overall contamination and for selected pathogens (such as Salmonella, Shigella, *Escherichia coli* and Campylobacter for food and *E. coli*/faecal indicators for surfaces and water), using standard laboratory protocols (of conventional culture and PCR). Part of the samples collected are used for lab analysis and the remaining part stored under −20°C for future analysis and crosschecking.	Subsample (approximately one-third of full cohort in each country)

ASF, animal source foods; WASH, water, sanitation and hygiene.

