### Data management and analysis

Data are collected at the households in CommCare and checked for accuracy before being transmitted to a central repository and can be downloaded in Excel for analysis. Samples are analysed at laboratories in each of the countries using tailored standard operating procedures.

Descriptive, comparative and regression analyses will be used to investigate the impact of WASH and food safety on child stunting. Factors relating to WASH and food safety amenities and practices will be considered simultaneously as external risks or preventive factors influencing the incidence and severity of stunting, using multivariable statistical approaches. To relate the main exposure variables (WASH and food safety factors) with the main outcome (stunting, measured as either z-scores or presence/absence), multivariable regressions models will be developed. According to our causal framework presented in figure 1, we will adjust this model for potential confounding factors. Some of these confounding factors will be fairly stable (eg, sex, maternal literacy, household facilities, socioeconomic status) and others will be time-varying (eg, age, breastfeeding, environmental hygiene levels). We will avoid intermediate factors (eg, infection rates). Subsequently, we will explore the potential role of the mediators in the causal framework using mediation analysis. Due to the existence of repeated measures conducted over three different time points for each child, we will account for this with a random effect term by individual in the regression model. The model will be a linear regression for stunting measured as a continuous variable, and a logistic (or ordered logistic) regression for stunting (moderate and severe) measured as a dichotomous variable. Due to the fact that in our three country settings the relevant association might differ, we will estimate the models separately in each country, and afterwards we will conduct individual participant data meta-analysis of the coefficients of interest across the countries. This strategy will allow for an optimal fit of the model in each country and at the same time we will be able to explore the heterogeneity of coefficients across countries and within subgroups (by age, sex and socioeconomic characteristics).

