The data generated from the study will help pave the way for future interventions to manage factors associated with and aimed at preventing stunting. At the individual level (immediate causes), inadequate practices and knowledge gaps identified will help tailor education and social behaviour change communication interventions. These are aimed at improving intake while reducing disease risks. At the household level (proximate causes), the findings can inform the implementation of more efficient WASH interventions, that ensure healthy environments and better personal hygiene. Ultimately, it can inform advocacy efforts to improve infrastructures and services at the community, regional or even national level (underlying causes).

ASF value chains generally present important potential to improve availability, accessibility, affordability and safety for the most nutritionally vulnerable population groups.^36^ This study can provide information on mechanisms through which value chains are linked to stunting. The study also offers information that will help to identify entry points in chains where upgrading may be feasible and agreeable among stakeholders (eg, consumers, government and businesses). Based on secondary dietary and nutritional data, a systematic literature review of food safety hazards in ASF value chains in each study setting and local experts’ feedback, commodities of likely relevance are eggs in all countries, milk in India and Senegal, and fish in Indonesia (see AASH food system protocol description in Cooper *et al* in this supplement for value chain work).

All in all, the described data, combined with data from other workstreams related to epigenetics, microbiome, gut health and nutrition, education, etc also described in this supplement, this work aims to providing with a powerful piece of evidence for improving the child environment with a ‘Whole child’ approach.

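### The stated model has a random effect for the child only; for exposures and outcomes that both cluster by area, confidence intervals may be too narrow

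*Protocol article*

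**What the plan says.** Under Data management and analysis, the protocol article plans multivariable regression of stunting on water, sanitation and hygiene (WASH) and food safety factors: linear for z-scores, logistic or ordered logistic for categories. It then fixes the dependence structure: "we will account for this with a random effect term by individual in the regression model". The only reason it gives is that every child is measured on three occasions. Those occasions are set under Data collection: "The interviews and spot-checks take place simultaneously during home visits at 9, 12 and 18 months after birth".

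Country is the only higher level mentioned: "we will estimate the models separately in each country, and afterwards we will conduct individual participant data meta-analysis". The article names no village, neighbourhood or sampling-area term and no cluster-robust variance.

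On where exposures arise, the Conceptual framework says of water: "Drinking water may be contaminated at the point of supply, or through transport and storage". It also says that food can become unsafe along the value chain before it reaches the home. The Discussion says of the findings that "it can inform advocacy efforts to improve infrastructures and services at the community, regional or even national level (underlying causes". On the other side, Table 2 records sanitation, handwashing and food storage facilities for each household and samples the household's stored water. Study design leaves the sampling process to a companion cohort paper.

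**The concern.** A child-level intercept absorbs the correlation among one child's three visits. Given the covariates, it still treats two neighbouring children as independent. Each country contributes one site with 500 households, so some children probably live close enough to share a water point, a market or a level of infection pressure. If so, an exposure such as water source type is partly the same observation counted many times, and its standard error is too small.

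The exposures most open to this are the supply and infrastructure items, which are also those closest to the use in advocacy that the Discussion foresees. If the country results are later compared or pooled using their standard errors, understated errors would also make countries look more different than they are.

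**Working it through.** **Inputs from the article.** 500 households per country; three visits per child; one random effect, for the child; models fitted by country. The article gives no ICC, no number or size of areas and no derivation of the 500, so it has no figure to reproduce.

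**Assumed inputs.** m = study children per area; rho_y = area ICC of the outcome residual; rho_x = area ICC of the exposure.

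**Formulas** (Moulton factor for an omitted level):
- DEFF = 1 + (m − 1) × rho_x × rho_y
- ratio of stated to correct interval width = 1/√DEFF
- true coverage of a nominal 95% interval = 2Φ(1.96/√DEFF) − 1

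| m | rho_y | rho_x | DEFF | Width ratio | Coverage |
|---|---|---|---|---|---|
| 5 | 0.01 | 0.1 | 1 + 4 × 0.001 = 1.004 | 0.998 | 95.0% |
| 10 | 0.02 | 0.3 | 1 + 9 × 0.006 = 1.054 | 0.974 | 94.4% |
| 10 | 0.02 | 1 | 1 + 9 × 0.02 = 1.18 | 0.921 | 92.9% |
| 20 | 0.05 | 0.6 | 1 + 19 × 0.03 = 1.57 | 0.798 | 88.2% |
| 25 | 0.05 | 1 | 1 + 24 × 0.05 = 2.20 | 0.674 | 81.4% |

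The first two rows stand for household practices with little clustering, and the last for an exposure identical within each area. Larger areas or ICCs give worse results (m = 20, rho_y = 0.10, rho_x = 1: DEFF 2.90, coverage 75.0%), but nothing in the article points to them.

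**Check by simulation.** The set-up was 500 children in 25 areas of 20, three visits, a child-constant exposure, a continuous outcome and 2000 runs per scenario.
- At rho_y = 0.05 and rho_x = 0.6, coverage was 86.1% with the child effect alone and 93.9% with area-clustered errors. The formula is approximate, and the simulated value lies about two points below its 88.2%.
- With either ICC at zero, child-only coverage stayed between 94% and 96%. Both must be positive for any harm.
- Across scenarios, uncorrected area-clustered errors covered 91% to 95%. With about 25 areas they therefore need a small-sample correction.

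**Limits.** These figures apply to a linear model with an exposure that is constant within the child. Direct observation and biological sampling cover about a third of the cohort. If that subsample is spread evenly over areas, m is about a third as large and the inflation is smaller. The article does not say how it is spread.

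**The case against.** The strongest reply is that the random-effect sentence serves a limited purpose, which is to handle repeated measures. It does that correctly and does not exclude further levels. A condensed article may leave these to a fuller plan, and the sampling process is expressly elsewhere. This stands in part: nobody can tell from the article whether recruitment was clustered, how many areas there are or how large they are. But the article does state its dependence structure and the reason for it, and that reason covers only visits within a child. Adding an area level improves on a stated model.

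A reader might infer something stronger: that water, sanitation and animal source food supply are shared within communities, so that intervals for WASH exposures in general will be too narrow. The documents do not support that:
- No section says that supplies are shared. The water sentence in the Conceptual framework also names transport and storage, which can differ from home to home.
- Table 2 measures sanitation and stored water at the household and assigns food hazards before the home to a separate value chain component.
- The 81% figure needs an exposure identical for all children in an area. Most questionnaire, spot-check, swab and food items will vary within areas.
- The relevant outcome ICC is the one left after adjustment for socioeconomic status, maternal literacy and household facilities, which may lower it.

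A reader might also infer that understated errors distort inverse-variance weights in the pooling. The article plans an individual participant data meta-analysis of coefficients but specifies no weighting, so that effect is only possible.

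**Conclusion.** The point holds conditionally. The stated model covers correlation within a child and leaves correlation between children of the same area unmodelled. Where exposure and residual outcome both cluster by area, intervals may be too narrow. Under the assumed values in the main table, the loss runs from negligible (94–95% coverage) for practices that vary between neighbours to about 81% coverage, with standard errors about 33% too small, for an exposure uniform within areas of 25 children at an outcome ICC of 0.05. If either ICC is zero, nothing is lost. All values of m, rho_x and rho_y are assumptions. This is a cheap improvement worth making, and no demonstrated error in any reported figure.

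**What to change.** In each country model, linear and logistic, add a random intercept for area (village, neighbourhood or sampling unit) above the child intercept. Alternatively, use standard errors clustered on area, with a small-sample correction if areas are few. Do the same in the pooled model, with areas nested in countries. Name the area unit for each site and report the area-level ICC of the outcome, so that readers can see whether the adjustment mattered.

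The cost is small. Households are visited at home, so area should be recoverable without new data collection. Intervals for area-patterned exposures become somewhat wider: at a design effect of 1.57, 500 children carry the information of about 318 (500/1.57). For exposures that vary mainly between neighbours, or if the ICC proves close to zero, little changes.

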### Patient and public involvement statement

Study participants have not been involved in the general design of the study. However, the study was designed in partnership with local research partners and stakeholders with experience in working at each of the settings. Local enumerators helped finalise the data collection tools during training and pilot testing.

Extensive consultations will be organised with the local communities to understand the ethos of the research including the involvement of participants and the implications of the research. Question and answer sessions will be held during the consultations to answer any questions and/or concerns raised. Study participants and the public will be involved in the dissemination of the study’s findings through community discussion or engagement events.

## Discussion

Poor food safety and inadequate WASH, including getting in direct contact with animals, their produce and/or their faeces, are considered as important contributors to undernutrition. Cumulatively over the first 2 years of life, these factors can determine linear growth faltering. However, the causes of infant stunting are not exclusive to these factors, and therefore, it is critical to cohesively consider the myriad of determinants involved. The UKRI GCRF AASH is using an interdisciplinary approach to investigate this variety of factors causing stunting with the aim to identify solutions for the amelioration of growth and development in early childhood at the ‘whole-child’ level. Within such an interdisciplinary framework, this study design will generate comprehensive evidence on the contribution of WASH, and food safety at the household level.

Challenges to conducting integrated assessment in WASH and food safety in a multicountry study like this are various, including identifying key ASFs and key hazards in a systematic way, or the analysis of pathways linking hygiene, food and water safety, and sanitation data into the typologies of stunting. For this purpose, we developed holistic data collection tools relevant to each study setting, to measure risk factors for exposure to foodborne and waterborne disease. Multiple household-level interventions are available in both WASH and food safety but, to date, their effectiveness has not been assessed together, despite the similarity in the exposure mechanisms they are targeting. The effectiveness of relevant interventions and technologies in addressing malnutrition depends on both their biological efficacy, and the degree to which consumers adapt to and use the new approach to their contexts.^8^ We propose an approach and suggest data collection tools through which these various underlying and proximate determinants of child growth may be analysed.

The data generated from the study will help pave the way for future interventions to manage factors associated with and aimed at preventing stunting. At the individual level (immediate causes), inadequate practices and knowledge gaps identified will help tailor education and social behaviour change communication interventions. These are aimed at improving intake while reducing disease risks. At the household level (proximate causes), the findings can inform the implementation of more efficient WASH interventions, that ensure healthy environments and better personal hygiene. Ultimately, it can inform advocacy efforts to improve infrastructures and services at the community, regional or even national level (underlying causes).

ASF value chains generally present important potential to improve availability, accessibility, affordability and safety for the most nutritionally vulnerable population groups.^36^ This study can provide information on mechanisms through which value chains are linked to stunting. The study also offers information that will help to identify entry points in chains where upgrading may be feasible and agreeable among stakeholders (eg, consumers, government and businesses). Based on secondary dietary and nutritional data, a systematic literature review of food safety hazards in ASF value chains in each study setting and local experts’ feedback, commodities of likely relevance are eggs in all countries, milk in India and Senegal, and fish in Indonesia (see AASH food system protocol description in Cooper *et al* in this supplement for value chain work).

All in all, the described data, combined with data from other workstreams related to epigenetics, microbiome, gut health and nutrition, education, etc also described in this supplement, this work aims to providing with a powerful piece of evidence for improving the child environment with a ‘Whole child’ approach.

